### Adverse events

Adverse events will be reported by the study’s executive committee to an independent Data and Safety and Monitoring Board (DSMB). The DSMB will have the authority to stop the trial early if patient safety is compromised or if the primary research objective is met. If the presumed 5% statistically significant difference in EF was achieved, it would be considered as reaching the primary objective of the study. A stringent statistical threshold would be used as the stopping rule. All safety issues (unanticipated SAEs, mortality, intracoronary infusion complications, severe arrhythmias, etc.) will be monitored by the DSMB, and the DSMB statistician will report the occurrence of safety issues in each study group quarterly. All deaths will be reported. Auditing would be done by DSMB on a 6-month interval and is independent of investigators.

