**Methods:**

This single-blinded, randomized, multicenter trial aims to establish whether the intracoronary infusion of umbilical cord-derived Wharton’s jelly MSCs (WJ-MSCs) helps prevent HF development after AMI. The study will enroll 390 patients 3 to 7 days following AMI. Only patients aged below 65 years with impaired LV function (LVEF < 40%) will be included. They will be randomized (2:1 ratio) to either receive standard care or a single intracoronary infusion of 10^7^ WJ-MSCs. The primary outcome of this study is the assessment of HF development during long-term follow-up (3 years).

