### Intervention

This study will use cGMP-certified clinical-grade human WJ-MSCs (Cell Tech Pharmed Co. Ltd., Tehran, Iran). The cells will be transferred to the hospital on the same day as the infusion and are to be suspended in normal saline (0.9%). Each batch will be analyzed and certificated by a qualified individual, ensuring that the cells comply with the product specifications. Standard operational protocols will be followed during shipment and handling.

In the intervention group, all 130 patients will receive a single intracoronary infusion of 10^7^ WJ-MSCs alongside the conventional treatment that will be provided to the same number of patients in the control group. Patients in the intervention group will be taken to the cardiac catheterization lab, where the infusion of 10^7^ WJ-MSCs will be done through the intracoronary route. A bolus heparin dose (weight-based) is to be administered to patients with an activated clotting time below 200 seconds.

For catheterization, we will insert a therapeutic 6 Fr guiding catheter into the left coronary artery. Following the infusion of nitroglycerin (200 μg) through the catheter, we will assess the left anterior descending (LAD) artery and document the TIMI flow. A 0.014-inch soft-tipped guidewire wire will be inserted into the LAD at the distal edge of the stent. After passing through an over-the-wire balloon to the stented area, the balloon will be inflated until achieving occlusion. Following the removal of the guiding wire, we will connect an infusion syringe to the infusion catheter. WJ-MSCs will be infused at a rate of 2.5 ml/min and the total sample volume would be 7.5 cc. Low-pressure inflation (2–4 bar) will be performed to achieve occlusion with the balloon catheter, with complete coronary artery occlusion being ensured ahead of cell infusion through the use of dye. After the infusion of each third of the cells, we will pause the infusion, and TIMI coronary flow will be assessed with the contrast agent before the resumption of cell infusion. Once the cells are delivered across the three portions, we will place the coronary flow wire via the microinfusion catheter. No methods were used to increase adherence for this intervention as it was a one-off treatment with no need for continued adherence.

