### Trial status

We began enrolling patients in Jan 2021 and expect to finish the recruitment process by Nov 2022. Data will be collected until Nov 2024. Thereafter, the analysis will be conducted. Results are expected to be ready by Dec 2024. We will prepare and submit the related manuscript following the CONSORT guidelines. This study is registered with *ClinicalTrials.gov* under the code NCT05043610. This protocol (version 1) was approved in Oct 2020. Changes in protocol will be submitted to the registration site.

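### The DSMB may end the whole trial for efficacy: on the written EF trigger that could leave about 3 to 8 of some 33 expected HF events, and on an HF trigger it could in practice only cut follow-up short

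*Protocol article*

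**What the plan says.** On early stopping, the Adverse events section gives the DSMB this power: "The DSMB will have the authority to stop the trial early if patient safety is compromised or if the primary research objective is met". It then defines the efficacy trigger: "If the presumed 5% statistically significant difference in EF was achieved, it would be considered as reaching the primary objective of the study". The threshold is described only in words: "A stringent statistical threshold would be used as the stopping rule". No schedule of efficacy looks is given. The same section mentions two other rhythms: "Auditing would be done by DSMB on a 6-month interval", and a DSMB statistician who will "report the occurrence of safety issues in each study group quarterly".

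Elsewhere the design is built on HF. The Abstract says: "The primary outcome of this study is the assessment of HF development during long-term follow-up (3 years"). Statistical analysis compares HF by Cox regression at two-sided P<0.05 and calls EF the secondary outcome. Under Intervention, "all 130 patients will receive a single intracoronary infusion", and eligibility requires a first infarct 3 to 7 days earlier. Under Trial status, "We began enrolling patients in Jan 2021 and expect to finish the recruitment process by Nov 2022", with data collection to Nov 2024. Follow-up and endpoints places echocardiography at six months and at the final visit.

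The article does not say whether randomised patients would still be followed after an efficacy stop.

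**The concern.** An efficacy stop helps trial participants only by changing what later participants receive. Here each patient's treatment is decided once, within days of the infarct, so that benefit ends when recruitment ends. After Nov 2022 the only thing left to stop is follow-up, which is where the 3-year HF outcome, the 3-year EF outcome and late safety come from.

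Before Nov 2022 the difficulty is different. A stop would come when few HF events have occurred, and the article lets EF, a secondary outcome, bring it about. Either way the trial could end without a usable answer to its 3-year HF question, or with one selected for being extreme.

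**Working it through.** **Inputs from the article.** HF at 3 years 12% control and 3.9% intervention (Sample size; these reproduce as 3 × 4% and 3 × 1.3%). N = 390, 2:1, with 130 infused. Recruitment Jan 2021 to Nov 2022, about 22 months. Data to Nov 2024, month 46. EF at six months.

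**Assumptions.** 260 control and 130 intervention, uniform accrual (390/22 = 17.7 a month), constant hazards, no dropout, efficacy looks every 6 months. The stringent threshold is taken as P<0.001 to P<0.01 for HF and P<0.001 to P<0.005 for EF. The 5% is read as 5 EF points, with SD 8 to 12.

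**1. HF events by calendar time.** Monthly hazards are −ln(0.88)/36 = 0.00355 and −ln(0.961)/36 = 0.00111, ratio 0.31. For month t up to 22, expected events in an arm of n are (n/22) × [t − (1 − e^(−λt))/λ].

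| Month | Control | Intervention | Total |
|---|---|---|---|
| 12 | 3.0 | 0.5 | 3.4 |
| 18 | 6.7 | 1.0 | 7.7 |
| 22 (recruitment closes) | 9.9 | 1.6 | 11.5 |
| 46 (each patient capped at 36 months) | 28.5 | 4.6 | 33 |

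Flat yearly rates of 4% and 1.3% give 3.3, 7.4 and 11.0 at months 12, 18 and 22.

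**2. The written trigger (EF).** Patients with a six-month EF number 17.7 × 6 = 106 at month 12 and 17.7 × 12 = 213 at month 18. At those times 177 patients (59 infusions) and 71 patients (24 infusions) are still to come. At month 18 with SD 10, SE = 10 × √(1/141.8 + 1/70.9) = 1.454. A true 5-point difference gives 5/1.454 = 3.44. Power is Φ(3.44 − 3.29) = 56% at P<0.001 and Φ(3.44 − 2.81) = 74% at P<0.005.

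| Single-look power (P<0.001; P<0.005) | Month 12 | Month 18 |
|---|---|---|
| SD 8 | 40%; 59% | 84%; 93% |
| SD 10 | 20%; 35% | 56%; 74% |
| SD 12 | 10%; 22% | 34%; 52% |

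With looks at both months, simulation gives a stop before recruitment closes in 85 to 94% of trials (SD 8), 57 to 75% (SD 10) and 34 to 55% (SD 12). If the observed difference must itself be at least 5 points, no single look can exceed 50% when the true difference is 5. The month-18 range is then 34 to 50%.

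If follow-up ended at such a stop, 3.4 to 7.7 HF events would be in hand, against 33. If only recruitment ended, a month-12 stop would fix the trial at 213 patients. Full 3-year follow-up of all 390 gives 260 × 0.12 + 130 × 0.039 = 36.3 events, so 213 patients give at most 213/390 × 36.3 = 20. The Schoenfeld requirement for 80% power is (1.96 + 0.84)² / [(1/3)(2/3)(ln 0.325)²] = 28.

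**3. A hypothetical HF trigger.** With equal exposure per patient, an all-control split reaches two-sided P<0.001 only at 19 events: 2 × (2/3)^19 = 0.0009, while 18 events give 0.0014. Only 11.5 events are expected when recruitment closes. Simulation with an exact conditional test and looks at months 6, 12, …, 42 gives:

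| Look threshold | Trials stopped | Stops before recruitment closes | Median HR at stop (true 0.31) | Stops at month 36 or 42 |
|---|---|---|---|---|
| P<0.001 | about 17% | none | 0.08 | 77% |
| P<0.01 | about 45% | 1 to 2% of stops | 0.15 | 58% |

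A log-rank version (true rate ratio 0.325) stops less often, 7.9% at P<0.001 and 25.7% at P<0.005, with the same pattern: 0.0 to 0.1% of trials stop before recruitment closes, and the median ratio at a stop is 0.11 to 0.16.

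**4. Type I error under the HF trigger, final test kept at 0.05.** 5.2 to 5.3% with looks at P<0.001, 6.4% at P<0.005, about 8% at P<0.01.

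**The case against.** A reader might infer that any efficacy stop must come after the last infusion and must exaggerate the HF effect. The article does not support that. Its only written trigger is EF, which is available from about mid-2021 and can fire while 24 to 59 infusions remain. An EF stop selects on EF and biases HF only through a correlation that the article does not give. Both statements hold for an HF trigger only.

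Four further objections have weight.

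- **Follow-up.** The article does not say that it ends with the stop. That is true, and for a stop during recruitment the loss is an assumption. For a stop after Nov 2022, nothing else is left to stop.
- **Size of the loss.** Most HF-triggered stops fall at month 36 or 42 of 46, and a month-42 stop costs four months. The timetable already gives the last patient only about two years. This objection stands, and it limits the harm on that branch.
- **Looks and threshold.** These commonly sit in an analysis plan or DSMB charter that is not shown, and the six-monthly audits are not stated to be efficacy looks. This stands, so their absence is not the point here and the type I error argument is minor. It does not undo the protocol's own power to stop the whole trial.
- **Use of the remedy.** Power to close recruitment on HF would almost never be used. That is also true. It shows how little an HF-based efficacy stop could offer participants in this design.

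**Conclusion.** The point holds in limited form. The protocol authorises an efficacy stop of the whole trial without protecting the follow-up on which its primary outcome depends.

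- **As written (EF trigger):** a stop at month 12 to 18 is plausible if the true EF difference is about 5 points. If follow-up ended with it, about 3 to 8 of some 33 expected HF events would remain, too few to answer the primary question.
- **If the trigger were HF:** a stop would come almost only after the last infusion and would report an effect far stronger than the truth, usually at the cost of a modest amount of follow-up.

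The event counts rest on the article's own rates and dates plus uniform accrual and constant hazards. The stopping probabilities and hazard ratios also rest on assumed looks, thresholds and EF standard deviations. This should be changed, but it does not invalidate a trial that runs to its planned end.

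**What to change.** In the Adverse events section, replace the efficacy half of the stopping authority, and the sentence that defines it by EF, with wording such as: An efficacy finding, judged on the primary endpoint of HF and not on EF, may at most close recruitment. All randomised patients are followed to the planned end of follow-up, and the confirmatory HF analysis is done once, at that point, at two-sided 0.05. Leave the safety stop as it is, and carry the same text into the DSMB charter.

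Excluding EF is essential. If an EF signal could close recruitment, the trial might be fixed at about 213 or 319 patients instead of 390.

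The cost is a short amendment to the protocol and charter. The one downside is that a very large early benefit would be reported later.

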### Follow-up and endpoints

Patients will receive daily visits from a cardiologist during hospitalization. The results of all physical examinations will be recorded, and patients will be monitored for early manifestations signaling arrhythmia, pulmonary embolism, or coronary artery injury. Blood tests will be done to measure fasting blood sugar, complete blood count, C-reactive protein, urea and electrolytes, liver function test, creatine kinase, and cardiac troponin T. An electrocardiogram (ECG) will also be obtained. Prior to the MSC infusion process, the cardiac evaluation will be completed using echocardiography. The initial EF will be established according to the wall motion score and Simpson’s rule. After the MSCs are delivered, once stable, a beta-blocker, angiotensin-converting enzyme (ACE) inhibitor, aldosterone antagonist, aspirin, ticagrelor, statin, and glyceryl trinitrate (spray or tablets) will be prescribed for the patient to use at home. A cardiac rehabilitation program will also be completed. Subsequent visits will be at ten days after discharge and then every three months when an ECG and blood tests will be requested. Echocardiography will be done during the six-month follow-up and the final visit, facilitating the evaluation of LV systolic function.

Our primary endpoint to assess the efficacy of the intervention will be the incidence of HF. Secondary endpoints include the improvement in LV function (through calculation of LVEF) after six months and after three years alongside echocardiographic changes in the left ventricular mass, left ventricular end-diastolic volume, left ventricular end-systolic diameter, and global longitudinal strain (measured via automated formulas in standard views) indices.

Data will be entered, encoded, became secure, and stored in a local database.

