### Statistical analysis

Data will be kept anonymous until analysis, which is to be performed by an independent statistician external to the research group. Continuous variables will be summarized using the mean and standard deviation, while frequencies and percentages will be given for categorical data. The analysis will follow the intention-to-treat approach. Two-sided P-values will be used and a *P*<0.05 will be considered as significant.

The primary endpoint of the study which is the incidence of heart failure will be compared between groups using Cox regression analysis.

We will consider the EF to have improved significantly if a minimum increment of 3% is achieved after six months. The EF, as the secondary outcome, will be compared between the study groups using the independent t-test.

The baseline characteristics of the two study groups will also be compared using independent sample *T*-test.

Safety will be compared between the two groups according to the occurrence of MACEs (death, recurrent AMI, ICD insertion, non-target vessel revascularization, etc.) and serious adverse events (SAEs) using COX regression analysis. These events will be followed over time with Kaplan-Meier curves, which will allow us to understand their patterns.

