## Discussion

Currently, the primary focus of post-AMI treatment is to prevent remodeling and avert any further loss of myocytes [5]. However, a revolution can potentially be achieved by regenerative medicine, aiming to restore cardiac function by inhibiting and even reversing the process of remodeling through the use of stem cells [24]. Even though some investigations were not very promising in this regard [8], other studies have shown that stem cell therapy may be of value in certain populations.

Although a Cochrane meta-analysis revealed that the LVEF of young AMI patients does not increase following BM-MNC therapy, survival and functional benefits may be present [23]. Importantly, research with MSCs has yielded more promising results, with the TAC-HFT trial indicating the roughly twofold higher efficacy of MSCs relative to BM-MNCs [19]. According to meta-analyses of the various clinical trials, MSCs can improve the LVEF by 5.72% [25], while BM-MNCs can achieve an inferior improvement of 3.07% [26].

Currently, scientists are yet to understand the exact mechanisms behind the therapeutic impact of stem cells, especially MSCs. However, the most commonly suggested mechanism is paracrine signaling, where the implanted stem cells alter the activity of the nearby cells in the heart via mediators like cytokines [28]. Also, it is still unclear whether or not the mechanical improvements in LV function after MSC transplantation would be translated into a clinical benefit by reducing major cardiovascular events. Our trial provides essential insights into the field by including selected patients who develop reduced LVEFs after AMIs.

Our trial, enrolling 390 patients, would be the largest clinical trial ever conducted in the field of regenerative medicine on myocardial infarction. We hope it would help clarify whether MSC transplantation is clinically useful or not.

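### The DSMB stopping rule counts a significant EF difference as meeting the primary objective, although heart failure incidence is the declared primary endpoint and EF is secondary

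*Protocol article*

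**What the plan says.** The endpoint hierarchy is stated plainly. Follow-up and endpoints: "Our primary endpoint to assess the efficacy of the intervention will be the incidence of HF". Statistical analysis: "The primary endpoint of the study which is the incidence of heart failure will be compared between groups using Cox regression analysis", and on EF: "The EF, as the secondary outcome, will be compared between the study groups using the independent t-test". The Abstract gives HF development over three years as the primary outcome, Study design frames superiority in terms of HF incidence, and Sample size is calculated on HF rates only.

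The Adverse events section then gives the DSMB two grounds for stopping: "The DSMB will have the authority to stop the trial early if patient safety is compromised or if the primary research objective is met". The second ground is defined in the next sentence: "If the presumed 5% statistically significant difference in EF was achieved, it would be considered as reaching the primary objective of the study". One qualifier follows: "A stringent statistical threshold would be used as the stopping rule". No value is attached to it.

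The Discussion describes the link between EF and outcome as open: "it is still unclear whether or not the mechanical improvements in LV function after MSC transplantation would be translated into a clinical benefit".

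**The concern.** The efficacy stopping rule names a different endpoint from the one the trial is designed, sized and analysed on. A DSMB following the text could conclude that the primary objective has been reached on a secondary echocardiographic measure, with no finding on HF at all. The article itself says that no study has yet tested MSCs on a clinical endpoint such as HF (Hypothesis generation), and that the step from better LV function to clinical benefit is unproven.

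The two endpoints also mature at very different speeds. EF is measured at six months and at the final visit, while HF events accrue over three years. If the six-month EF is the one intended, the EF comparison can be decisive while the HF comparison still carries little information.

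**Working it through.** **1. Status of each endpoint in the protocol article**

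| Section | HF incidence | EF |
|---|---|---|
| Abstract, Methods | primary, 3 years | – |
| Study design | object of the superiority question | – |
| Sample size | sole basis | not used |
| Follow-up and endpoints | primary | secondary |
| Statistical analysis | primary, Cox regression | secondary, t-test |
| Adverse events (DSMB) | not mentioned | meets the primary objective |

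No section reconciles the last row with the others.

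**2. The plan's own HF figures**

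The three-year rates are three times the one-year rates: 3 × 1.3% = 3.9% and 3 × 4% = 12%. With R = 2, a difference of 0.081 and an average rate of (0.12 + 2 × 0.039)/3 = 0.066, the printed formula gives 1.5 × 0.066 × 0.934 × 2.8² / 0.081² = 110.5 for the smaller arm and 331.5 in total. The stated total is 328, so the agreement is close. It is reached only with double weight on the intervention rate, which is a separate matter. What counts here is that no EF effect enters the calculation.

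The final size is 390 with 130 treated, hence 260 controls. Planned HF events: 130 × 0.039 + 260 × 0.12 = 5.1 + 31.2 = 36.3.

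**3. Information available at month 18**

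Month 18 is an illustration. Assumptions: uniform accrual over the 22 months from January 2021 to November 2022 (Trial status), and constant hazards.

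- Enrolled: 390 × 18/22 = 319.
- With a six-month echo: 390 × (18 − 6)/22 = 213, split 71 treated and 142 control.
- Person-years: 319 × 9/12 = 239.
- Annual hazards: −ln(0.88)/3 = 0.0426 (control) and −ln(0.961)/3 = 0.0133 (treated). Pooled at 2:1: (2 × 0.0426 + 0.0133)/3 = 0.0328.
- Expected HF events: 239 × 0.0328 = 7.9, about 8 of 36 (22%). With the flat annual rates of 4% and 1.3%, the count is 239 × 0.031 = 7.4.

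**4. Chance that the EF trigger is met at month 18**

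The documents give no SD for EF, so 8 to 12 points is assumed, with a true difference of 5 points. SE = SD × √(1/71 + 1/142) = 0.1453 × SD. For illustration, stringent is taken as two-sided p<0.001 (critical z = 3.29). The chance of significance is Φ(5/SE − 3.29).

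| SD | SE | Critical difference | P(p<0.001) | P(p<0.001 and observed ≥ 5) |
|---|---|---|---|---|
| 8 | 1.16 | 3.8 | 84% | 50% |
| 10 | 1.45 | 4.8 | 56% | 50% |
| 12 | 1.74 | 5.7 | 34% | 34% |

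The last column takes the 5% as a floor on the observed difference. When the critical difference is below 5, the floor binds and the chance is one half. At SD 12 the critical difference exceeds 5, so the floor adds nothing.

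**5. What the HF comparison could show at that point**

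HR = ln(0.961)/ln(0.88) = 0.31, so |ln HR| = 1.167. Schoenfeld power at two-sided 0.05 is Φ(√(d × 1/3 × 2/3) × 1.167 − 1.96). For d = 7.9 this is Φ(1.55 − 1.96), about 34%. For d = 36.3 it is Φ(3.31 − 1.96), about 91%. The approximation is rough at 8 events, but the contrast is clear.

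**The case against.** Several points on the other side have force.

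- **Stopping is not automatic.** The DSMB has authority to stop and no obligation. This stands, but the text itself declares the objective reached and so invites the decision.
- **A stringent threshold is promised, and its value may sit in a charter.** Its absence from an article is no finding. However, a stricter p-value applied to EF is still a stop on EF. The threshold does mean that chances at p<0.05 (82–99% at month 18) should not be used, because the text rules out an ordinary 0.05 test for stopping.
- **The trigger is ambiguous.** The 5% may be a floor on the observed difference or a significance level, which is why two columns are shown. The section also does not say which EF measurement counts, so six months is an inference. On every reading the trigger is EF.
- **HF information need not be lost.** Treatment is a single infusion, and the text does not say that follow-up would cease. If the 319 patients enrolled by month 18 were followed for three years, the planned rates would give 319 × (2 × 0.12 + 0.039)/3 = about 30 events. A reader might infer that the HF comparison would be uninterpretable. That would require follow-up to end as well, which the article does not state.
- **The 5% has a visible source.** The introduction reports EF gains of about five points with MSCs. A reader might also infer a conflict with the Statistical analysis section: "We will consider the EF to have improved significantly if a minimum increment of 3% is achieved after six months". That sentence reads as a change over time and the DSMB sentence as a difference between groups, so a contradiction is not established.

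A reader might further take the trial's purpose to be learning whether EF gains become clinical benefit. The article states the purpose as reducing HF incidence and mentions the EF link only as an open question.

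**Conclusion.** The contradiction is real and rests on the wording alone. The DSMB paragraph equates the primary objective with an EF result, while every other section makes HF incidence primary or builds on it, and EF is labelled secondary. As written, the rule permits a declaration of success on the wrong endpoint, so it must be corrected.

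The practical size is conditional. If the six-month EF is used, about 8 of 36 planned HF events would exist at month 18, when the chance of p<0.001 on EF is about 34–84%, or about 34–50% with a 5-point floor on the observed difference. These figures assume uniform accrual, the planned HF rates, a true 5-point EF difference, an SD of 8 to 12 points and p<0.001 as the stringent level. The documents do not support saying that the trial would certainly stop, or that the HF question would certainly be lost. The loss depends on the DSMB's decision and on how far enrolment and follow-up end.

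**What to change.** Delete the sentence that equates an EF difference with the primary objective. Replace it with text along these lines: *Early stopping for efficacy will be based only on HF incidence, the primary endpoint, at a stringent pre-stated boundary (for example Haybittle-Peto, p<0.001). EF is reported as a secondary outcome and is not a reason to stop for efficacy.* The boundary named is one option; the essential change is the endpoint. The safety ground for stopping is unaffected.

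The cost is an amendment to the protocol and the DSMB charter, with the registry update that Trial status promises for protocol changes. Enrolment began in January 2021, so this is a change during the trial. It should be made without reference to comparative EF or HF results. It needs no extra patients or procedures.
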